##### CD4 and HIV VL testing only

We anticipate that approximately 700 participants who complete the baseline questionnaire and test HIV positive will be excluded from the intervention trial because they are already aware of their status and have linked to HIV care, or because there are multiple new HIV diagnoses within a household. These individuals will be offered participation in a “CD4 and VL testing only” group. Including this group will allow us to have HIV VL measures from all consenting new or known PLHIV in the included villages which provides us the ability to assess the population-level effects of the intervention. Study staff will obtain written informed consent for the collection of CD4, VL, and a brief questionnaire interview at 12-month follow-up. See Fig. 1 for a flowchart depicting the study procedures and sample size approximation per study arm.

#### HIV testing procedures

HBHCT will be conducted according to the MOH protocol for HBHCT [41] by study staff trained in HIV testing and counseling procedures. According to the protocol, counseling consists of pre-test counseling and giving results with post-test counseling. Pre-test counseling includes: reviewing the test process, discussing the understanding of potential test results, and assessing risk for HIV infection. Rapid tests will be used which provide results in approximately 15 min. In the measures section we provide details on the HIV testing algorithm. When the results are ready, the counselor will provide the test results to the individual (or couple if applicable). The information provided will depend on whether the test is positive or negative. If the result is negative, the counselor will discuss HIV prevention (condom use, ways to reduce risk) and encourage future testing. If the result is positive the counselor will provide supportive counselling, discuss disclosure (if applicable), emphasize the importance of partner testing (if applicable), discuss HIV care and treatment available at the nearest health facilities and the laboratory technician will take a blood sample for CD4 and HIV VL testing. After the counselor tells the client his/her HIV test results, for those who are newly diagnosed, counselors will provide linkage to care following either the standard-of-care (paper-based referrals) or the PATH/Ekkubo intervention protocol, as detailed in the following sections. Control counselors will be trained to deliver standard-of-care linkage only, and will work only in villages allocated to the control arm. The intervention counselors will be trained in the PATH/Ekkubo intervention protocol over a four-day training and will work only in intervention villages.

### Description of the study arms

#### Control arm: Standard-of-care linkage (see Table 1)

##### During HBHCT

In villages randomized to the standard-of-care arm, the control counselor will provide information on HIV care and treatment and provide the client with a referral to HIV care and a list of health facilities, including location and HIV clinic hours, in their area that provide free HIV care.

**Table 1 Tab1:** Linkage to care in the control arm: Standard-of-Care

Baseline HBHCT visit 10 min	Provide information on HIV care and treatment available including HIV clinic locations and hours and provide referral to care
Two-Week CD4 results home visit 15 min	Provide CD4 results and a paper-based referral to care. Explain logistics of how to get care and importance of accessing HIV care.

Note: Control arm activities follow standard of care for linkage referrals in Uganda. *HBHCT* home-based HIV counseling and testing

##### Two week CD4 results home visit

Two weeks after HBHCT, the control counselor will return to the participant’s home and provide them with their CD4 test results, and explain that they should take the CD4 results card with them when they present for HIV care. The counselor will also explain what the CD4 count means and if it indicates that they are eligible for ART, until the district adopts the MOH guidelines for immediate ART initiation, at which point they will be told they are eligible for ART regardless of CD4 test result. The two-week interval of return of CD4 results was the standard-of-care before “test and start” began to be adopted. With expansion of universal treatment, CD4 testing will no longer be a requirement for treatment initiation.

#### PATH/Ekkubo intervention arm: Enhanced linkage to care and treatment (see Table 2)

The intervention was originally developed and tested in a randomized trial with urban outpatients receiving opt-out HIV testing by [name] [39]. Due to logistical differences between outpatient opt-out testing and HBHCT, we have made adjustments to include additional counselling sessions, to encourage and facilitate disclosure and seeking social support to address HIV-related stigma to increase the intervention’s effect on multiple outcomes--beyond those examined in the previous trial. The development of stigma-reduction elements of the intervention were guided by the HIV Stigma Framework [42].

The overall goal of the PATH/Ekkubo intervention is to identify and reduce barriers to HIV care through multiple follow-up counseling sessions following HBHCT. The intervention content includes up to six sessions delivered over a 10-week period. The core components and session schedule are described in Table 2. The first session begins after post-test HIV counseling during the initial HBHCT home visit and subsequent sessions are at 2 weeks and 6 weeks post HBHCT with optional sessions at 8 and 10 weeks for those who have not linked to care by 6 weeks; in addition there is a booster counseling session at the clinic when the client first presents to the HIV clinic. The components of the intervention include: linkage to care and referral, provision of CD4 results during the two-week visit, orientation to the HIV care system and the assessment of potential for adverse effects related to HIV diagnosis and linkage to care (e.g., intimate partner violence). The counselor assesses needs and barriers to linkage (e.g., coping skills, social support, HIV-related stigma, and additional barriers), provides counseling and referrals to overcome identified barriers, and provides additional help planning for disclosure, seeking social support, and dealing with HIV-related stigma. Finally, the session ends with the elicitation of the client’s intention to seek HIV care. Each subsequent session includes reassessment of linkage status and barriers to care and counseling to overcome barriers, building on the counseling provided in the previous sessions. If at any point during the intervention period the client has linked to HIV care, the counselor aims to reinforce engagement in care and assess/reduce barriers to continued engagement.

**Table 2 Tab2:** Intervention arm: Enhanced Linkage to Care

	Intervention session core components
Session 1, Baseline home visit *Protocol Components 1-8* 30 min	1. Explain linkage to HIV care 2. Assessment of potential adverse effects 3. Assess needs/barriers to HIV care 4. Provide counseling to overcome barriers a. Assess HIV-related stigma b. Counseling to overcome stigma c. Identify sources of social support d. Provide referrals for social support e. Counseling to address other barriers 5. Help the client plan for disclosure, seeking social support, and HIV stigma a. Create a disclosure plan b. Identify treatment supporter(s) c. Encourage support seeking 6. Orient client to the HIV care system and process 7. Elicit client’s intention to seek HIV care 8. Set the time/date for two-week CD4 result home visit
Session 2, Two-week CD4 results home visit 30 min	1. Provide CD4 results and explain what they mean. If not eligible for treatment explain importance of repeat CD4 testing every 3 months 2. Review plans and discuss client’s plans from Session 1 3. Assess if client has linked to care 4. Assess the participant’s needs/barriers to care and provide counseling/referrals a. If patient has not been linked: As appropriate, repeat components 1-7 from Session 1 b. If patient has been linked: As appropriate, repeat components 1-6 from Session 1 in relation to continued linkage 5. Assess HIV-related stigma and if client has disclosed and sought social support. 6. As needed provide counseling on seeking social support 7. Assess and discuss disclosure 8. Discuss treatment supporter 9. Review barriers and plans for overcoming barriers and getting social support 10. Elicit client’s intention to seek HIV care/attend second clinic visit 11. Set the date/time for the next home visit
Session 3, Six-week home visit 30 min	Repeat steps outlined in Session 2
Session 4, First HIV clinic visit 30 min	1. Congratulate client on attending the HIV clinic 2. Assess client’s barriers to attending a second clinic visit 3. Assess if client sought social support and if needed provide counseling on seeking social support 4. Address any other barriers to care and any medical needs 5. Review barriers to care, plans for overcoming barriers and getting social support 6. Elicit intention to attend the next clinic visit
Optional Session 5 & 6, Additional visit/phone calls 30 min	Up to two calls those lost to follow up, repeat Session 3 If cannot be reached via phone, one home visit for those lost to follow up, repeat Session 3

### Data collection procedures and measures

Using a computerized structured questionnaire, a brief baseline interview will be conducted during the HBHCT visit for all participants consenting to HIV testing and interview. Following completion of the interview, the team will undertake HIV counseling and testing following the Ugandan MOH protocol for HBHCT [41]. If the result is positive and the participant has provided informed consent for enrollment in either the intervention trial or the CD4 and VL monitoring only group, the health worker will take blood for CD4 and HIV VL testing. Follow-up interviews will be conducted at six and 12-months follow-up for participants enrolled in the intervention trial, using a computer-based structured questionnaire (<60 min duration). The data collection schedule, procedures, and instruments will be identical in both study arms and follow-up interviewers will be blinded to study arm assignment. A brief, 12-month questionnaire will be administered with participants in the CD4 and VL only group. For both intervention trial and CD4 and VL groups, we and will also take a blood sample for CD4 and HIV VL testing at 12 months, which will be returned to all participants during a 14-month home visit. Additionally, study staff will abstract data regarding attendance at the HIV clinic, CD4 count, and treatment regimen from medical records at each of the participating clinics as a secondary data source for some of the study outcomes. Cost data will be collected from activity logs and accounting records, and through micro-costing of intervention activities. Details of the study variables, measures, and timeframe for collection are described below and in Table 3.
*HIV status* (baseline). Health workers will obtain a finger stick capillary blood sample to run the HIV rapid tests. Following WHO recommendations to assure HIV testing quality in high prevalence settings [43] and the Ugandan MOH recommended assays, the rapid HIV testing algorithm we will be using in the study is as follows: Determine HIV-1/2 Assay (Alere/ Abbott Laboratories, Chiba, Japan) as the first test in the algorithm. If Determine is non-reactive, an HIV-negative result will be reported. For those found reactive with Determine, a second test, HIV 1/2 STAT-PAK (Chembio Diagnostic Systems, Medford, NY, USA) will be performed. If reactive with STAT-PAK, results will be reported as HIV positive. If reactive with Determine and non-reactive with STAT-PAK, both the Determine and STAT-PAK tests will be repeated. If both the repeat Determine and repeat STAT-PAK are reactive, an HIV-positive result will be reported. If both the repeat Determine and repeat STAT-PAK are non-reactive, an HIV-negative result will be reported. If the repeat Determine is reactive and the repeat STAT-PAK result is non-reactive, the sample will be tested using Uni-Gold HIV (Trinity Biotech, Bray, Ireland). If Uni-Gold is reactive, an inconclusive result will be reported and the participant will be re-tested in 14 days. If Uni-Gold is non-reactive, an HIV negative result will be reported. For quality control purposes, a venous blood sample will be taken with every 10th participant who tests HIV negative. Deoxyribonucleic acid polymerase chain reaction tests will be performed on these specimens for quality control.

#### Primary outcome measures

*Individual and population HIV VL suppression* (baseline and 12 month). We will examine HIV VL suppression at two levels; VL <200 and as undetectable VL —defined as HIV RNA <20 copies/mL. We will also examine changes in VL between baseline and follow-up to determine reductions considered statistically significant—a threefold, or a 0.5 log_10_ copies/mL reduction [44]. Specimens for VL testing will be collected via venous blood draw at baseline and during the 12-month in-home follow-up interview. HIV VL testing will be performed on plasma processed at the Gombe Hospital Laboratory and subsequently sent to Uganda Virus Research Institute (UVRI). HIV VL testing at UVRI will be done using the Roche COBAS AmpliPrep/TaqMan assay (Roche Molecular Systems, Pleasanton, CA) which has a lower limit of detection of 20 copies/mL.

#### Secondary outcome measures

Our main secondary outcome measures include HIV care linkage, ART initiation, and short-term retention in care (detailed below) collected through participant self-report at six and 12-month follow-up interviews, supplemented by clinic records and direct observation of participants’ HIV clinic cards and ART pill bottles where possible.
*Linkage and time to care* (six and 12 months, clinic records). We will assess linkage to care with data on: enrollment in an HIV clinic, having a second HIV clinic visit, and time from HIV testing to enrollment in care at an HIV clinic.
*ART initiation & time to initiation* (six and 12 months, clinic records). To assess receipt of HIV treatment we will determine if participants have been prescribed and have taken ART and the time from HIV testing to ART initiation. We will determine the percentage of participants eligible for ART (currently CD4 < 500 until the guidelines [8] to expand eligibility are implemented nationwide), who received antiretrovirals (ARVs) based on their CD4 count taken at the time of HBHCT, as well as the time from diagnosis to ART initiation. If possible, interviewers will directly observe the participant having ARVs at their home and review the patient’s HIV clinic record card to confirm self-reported data.
*Short-term retention in care* (six and 12 months, clinic records)*.* We will assess the following retention measures that have demonstrated the best discriminatory capacities for predicting viral suppression [45, 46]: a) missed visit count: number of missed visits accrued (count measure) based on scheduled visits determined by MOH clinical guidelines, b) visit adherence: proportion of kept visits/scheduled visits (kept + missed visits) (continuous measure, range = 0.0–1.0), and c) four-month visit constancy: number of four-month intervals with at least one kept visit (categorical measure, range = 0–3).

#### Independent variables

*Sociodemographics* (baseline). We will assess participants’ gender, age, tribe, educational level, socioeconomic status, employment status, income, religion, gender, marital/partnership status, distance to clinic, and travel time to the clinic.
*Prior use of health services* (baseline). We will measure prior use of HIV services, including history of HIV testing, frequency, location, and reasons for health service use in the prior 6 months, male circumcision for men, and location of births for women.
*CD4 cell count* (baseline, 12 months)*.* CD4 cell count will be assessed via venous blood draws along with VL at baseline and 12-month follow-up. Baseline CD4 values may affect viral suppression success [47]. We did not include CD4 as an outcome measure because according to recommendations by WHO and the United States Department of Health and Human Services, when VL is available, CD4 has little added value for monitoring treatment adherence and efficacy of ART [44, 48].
*Tuberculosis (TB)* (six and 12 months, clinic records). We will assess co-infection with TB using questions adapted from the MOH’s HIV clinic card. Interviewers will use the participant’s clinic card and self-report to record if the participant is TB infected, date of diagnosis, and treatment initiation and regimen.
*ART adherence* (six and 12 months). We will assess self-reported adherence to ART using the Adult AIDS Clinical Trials Group scale [49], which includes recall questions about ARVs missed for the previous 4 days prior to the interview, as well as 17 items assessing participants’ main barriers to adherence. It has demonstrated construct validity in Uganda and similar settings [50].
*Disclosure of HIV-test results* (six and 12 months). We will measure HIV status disclosure with an instrument used in prior research in Uganda and other African countries [39, 51]. It asks about the disclosure of serostatus to spouses, sexual partners, family members, community members/leaders, physicians, etc. The proportion of participants reporting each disclosure is calculated after eliminating those who say the disclosure was not applicable to them.
*Receipt of instrumental and emotional social support* (six and 12 months). We will measure receipt of instrumental and emotional social support using the Social Support Scale [51], which contains six items on emotional support and four items on instrumental social support. This scale was adapted from the Duke-University of North Carolina Functional Social Support Questionnaire [52] and has been validated among PLHIV in rural Rwanda (α = 0.91) [53]. In addition, we will determine if participants have a treatment supporter, have attended HIV support groups, or been counseled by an HIV-positive peer educator, and how helpful each of these forms of counseling have been on a four point scale ranging from “not helpful” to “very helpful.”
*HIV stigma* (baseline, six, and 12 months). At baseline, for those individuals reporting they are HIV negative or do not know their HIV status, we will measure enacted stigma, including nine items on discrimination, stereotypes, and prejudice using Kalichman et al.’s [54] AIDS-related stigma scale, which has been validated in South Africa [54]. We will also measure anticipated stigma, asking participants how they would feel if they tested positive, using six items from Earnshaw’s [42] anticipated stigma scale and six items from Berger et al.’s [55] HIV stigma scale. We will calculate the mean of all participants from each village to get a village (cluster)-level HIV stigma score at baseline. At six and 12-month follow up, and at baseline for those who report already knowing they are HIV positive, we will assess the following dimensions of HIV stigma among PLHIV [56]: (a) anticipated stigma using six items from Earnshaw’s [42] anticipated stigma scale and two subscales from Berger et al.’s [55] HIV stigma scale: eight items assessing anticipated stigma related to disclosure and eight items assessing anticipated stigma related to concern with public attitudes about PLHIV; (b) enacted stigma using six items from Earnshaw’s scale [42], 16 items from the personalized HIV stigma subscale of Berger et al.’s [55] scale, as well as items from Sayles et al.’s [57] multidimensional HIV stigma scale: 12 items from the stereotypes subscale and seven items from the social relationships subscale; and (c) internalized stigma using Kalichman et al.’s [58] internalized AIDS-related stigma scale. All of these measures have shown good reliability among sub-Saharan African samples (α = 0.73-0.78) [59–61].
*Subjective health status* (six and 12 months). We will use the 36-item Medical Outcomes Study-HIV short form [62] to assess subjective health status adapted for the Ugandan context [63] and shown to be reliable among PLHIV in rural populations in Uganda (α > 0.70) [63, 64].
*Perceived need for HIV care/treatment* (six and 12 months). We will adapt five items used in a study in Zambia [65] to assess participants’ perceived need for HIV treatment. The items assess participants’ agreement with statements such as: “You do not need to go to the HIV clinic because you feel healthy” and “You do not want to take any medicine.”
*Barriers to care* (six and 12 months). We will measure barriers to attending HIV care, including distance/time to the clinic, financial barriers, work/child care responsibilities, wait times, and concerns with privacy among health workers. We will include 18 items adapted from the LifeWindows Information Motivation Behavioral Skills ART Adherence Questionnaire [66] and Smith et al.’s [67] scale on engagement and retention in pre-ART HIV care. We will also determine the actual distance and travel time from the participants’ home to the HIV clinic and for the cost of transportation to the clinic, for those who are able to pay.
*HIV care system literacy.* We will use nine items from the Brief Estimate of Health Knowledge and Action HIV Version scale [68] to assess participants’ knowledge of the HIV care system, including questions on where they can get treatment, the cost of treatment, treatment eligibility, etc.
*Beliefs about traditional and western medicine* (six and 12 months). We will assess beliefs towards western and traditional medicine and use of traditional medicine to treat HIV using items adapted from the treatment denialism subscale of Kalichman’s AIDS denialism scale [69].
*Relationship with the clinic provider*. We will measure participants’ satisfaction with their healthcare provider using 10 items from a scale used in South Africa by Westaway and colleagues [70].
*Acceptance of HIV diagnosis.* Three items modified from the Brief COPE Scale [71] will be used to assess participant’s acceptance of their HIV diagnosis by asking participants if they have refused to believe their test results since they tested positive.
*Alcohol use*. We will assess alcohol use using the Alcohol Use Disorders Identification Test [72], shown reliable among PLHIV in rural Uganda (α = 0.71) [73].
*Depression* (six and 12 months)*.* We will measure depression symptoms using a modified 20-item version of the Center for Epidemiological Studies scale [74], which has been shown to be reliable in a rural Ugandan sample (α = 0.90) [75].
*Positive and negative life events following HBHCT* (six and 12 months). We will include items to assess life events following HIV testing using items by Grinstead et al. [76] and used in our prior work in Uganda [39]. The scale assesses the occurrence of life events since diagnosis, such as the strengthening of a relationship, breakup of a relationship, physical abuse by a sexual partner, and neglect by family.
*History of intimate partner violence* (six and 12 months). Items assessing experience of intimate partner violence originating from the Conflict Tactics Scale [77] and included in the WHO multicountry study [78] will be included. The scale includes 10 questions asking participants if they experienced any emotional (e.g., has he/she ever insulted you or made you feel bad about yourself?), physical (e.g., has he/she ever kicked you, dragged you, or beaten you up), and sexual violence (e.g., has he/she physically forced you to have sexual intercourse when you did not want to?) from a partner ever, and in the prior 12 months.
*Intervention contamination* (six and 12 months)*.* We will ask participants what type of counseling they received and from whom (to assess potential contamination) and the number of HIV-positive household members and if they are in care and on treatment. We will keep records on the number of and duration of intervention sessions each intervention arm participant actually received.
*Clinic level factors* (twice monthly)*.* We will monitor ART and cotrimoxazole stock outs at the participating clinics and hospital, where participants will most frequently visit to pick up their medications, on a twice-monthly basis through use of a checklist that includes of all drugs routinely prescribed for HIV-positive individuals.

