### Limitations

Among the study’s limitations is the threat for contamination between intervention and control villages. However, randomizing at the level of the village and having villages assigned to different study arms not geographically close to one another should minimize this threat. We will monitor potential contamination by asking all study participants what kind of linkage counseling they received and from whom. Interviewers conducting the follow-up assessments will be blinded to study condition, however, un-blinding is possible if participants discuss the intervention with the interviewer. We will monitor this by debriefing interviewers. In addition to individual-level data, we will collect clinic-level data; cross-classification may occur if participants seek HIV care at a clinic other than the one nearest to them. However, our data analysis approach can accommodate cross-classification. Finally, in order for participants to be eligible for participation, they must be willing to accept home visits, which may limit the generalizability of the findings. However, we judge this to be only slightly more than in any study which tracks participants via home visits, and from prior studies, we have found that very few patients decline to participate due to the possibility of being visited at home.

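### The study's own counseling and cost questions are likely to un-blind the follow-up interviewers who collect the self-reported linkage, ART and retention outcomes, and the protocol concedes only un-blinding that participants start themselves

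*Protocol article*

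**What the plan says.** The Data collection procedures and measures section states that the "instruments will be identical in both study arms and follow-up interviewers will be blinded to study arm assignment". Under Independent variables, the intervention contamination entry, timed at six and 12 months, reads: "We will ask participants what type of counseling they received and from whom (to assess potential contamination". Limitations confirms that the item goes to everyone: "We will monitor potential contamination by asking all study participants what kind of linkage counseling they received and from whom". The Cost measures section adds 12-month questions on what participants spent in connection with the intervention and HIV care.

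On un-blinding, Limitations says only that "un-blinding is possible if participants discuss the intervention with the interviewer", to be monitored by debriefing the interviewers.

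On sources, Secondary outcome measures says that linkage, ART initiation and short-term retention are "collected through participant self-report at six and 12-month follow-up interviews, supplemented by clinic records and direct observation" of clinic cards and pill bottles where this can be done. Data collection describes abstracted clinic records "as a secondary data source for some of the study outcomes".

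**The concern.** The blinding statement and the contamination item pull against each other. Limitations treats un-blinding as something a participant might cause by chance, but the study plans to ask for the information that separates the arms. Debriefing can show that un-blinding happened; it cannot prevent it.

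This matters because the outcomes gathered at the same interviews depend largely on what participants say and how interviewers probe and code it. Linkage and ART initiation are main secondary outcomes. Aim 1 also names them as mediators of the effect on viral suppression, and the costing aim uses them as effectiveness measures. Reporting that differs by arm would distort all three uses.

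Two mechanisms need to be kept apart. Interviewer bias depends on the interviewer knowing the arm, and the order of items and staffing can reduce it. Participant reporting bias arises because participants know what counseling they had and were encouraged to seek care. It exists whatever the interviewer knows, and only verification of the reported events addresses it.

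**Working it through.** The protocol gives no figure to reproduce, so the first part of the check compares sections.

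**1. Does the item separate the arms?** Control participants receive information and a referral at the testing visit, then one counselor home visit at two weeks with CD4 results (Table 1: 10 and 15 minutes). Intervention participants receive up to six sessions, including home visits at two and six weeks and a session at the clinic (intervention arm description and Table 2). A full answer about type and source of counseling will usually point to one arm. It will not always settle it, because both arms have a two-week counselor visit.

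**2. Who asks it, and when?** Its timing and its place among the questionnaire measures suggest the follow-up interviewer. Table 3 does not list the item, and the article gives neither the order of items nor who administers it. Un-blinding is therefore likely, not established.

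**3. How far does it spread?** Villages are randomized, and the planned average is 14 enrolled participants per village. One revealing answer can disclose the arm for every later interview that the same interviewer does in that village, and for that interviewer's own return at 12 months. Asking the item last protects the outcomes of the current interview but not those later ones.

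**4. Which outcomes are exposed?** Linkage, ART initiation and retention are exposed through self-report. Viral load is a laboratory result from a venous sample and is not.

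**5. Illustration of size (over-report rates assumed).** Let p be true linkage, equal in both arms, and f the share of non-linkers who falsely report linkage in the intervention arm only. The spurious difference is f × (1 − p).

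- p = 0.58 (one of the linkage figures cited in Background): 0.10 × 0.42 = 0.042 and 0.20 × 0.42 = 0.084.
- For p of 0.42 (also cited there), 0.58 or 0.75 (assumed) and f from 0.05 to 0.20, the range runs from 0.05 × 0.25 = 0.0125 to 0.20 × 0.58 = 0.116.

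With 300 × (1 − 0.18) = 246 per arm and a two-sided 5% test of two proportions, the chance of a false positive favoring the intervention at p = 0.58 is as follows (nominal 2.5% in that direction):

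| f | Spurious difference (points) | Ignoring clustering | Design effect 1.5 (assumed) |
|---|---|---|---|
| 0.05 | 2.1 | 7% | 6% |
| 0.10 | 4.2 | 16% | 12% |
| 0.20 | 8.4 | 49% | 35% |

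These figures describe over-reporting by participants from any cause. They do not measure the extra bias due to an un-blinded interviewer, and they give record, card or pill checks no corrective effect.

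**6. Would records first, with self-report as fallback, remove it?** No. A person who never linked has no enrollment record, so the fallback would accept the false report and f × (1 − p) would be unchanged, unless a card or pill check blocked it.

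**The case against.** The best case for the protocol has four parts.

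- **Item order is detail for the full protocol.** An article need not give it, and if the item comes last, that interview's outcomes are already recorded. This stands as a limit on certainty. A reader might infer that blinding is sure to fail; the article does not support that, since it is silent on who asks the item and when, and control participants also have a counselor visit to report.
- **The risk is disclosed.** Limitations mentions un-blinding directly after describing the contamination question. That is true, but it ties the risk to participants' initiative and not to the study's own question.
- **Self-report does not stand alone.** Each of these outcomes is tagged with clinic records, Table 3 notes that both sources are used, and cards and pill bottles are checked when possible. This reduces the bias. The checks remain supplementary and conditional, and a rule for discordant sources may properly sit in an analysis plan that is not shown.
- **Records are incomplete.** They are abstracted at participating clinics, and Limitations foresees care elsewhere. Making records the lead source is therefore a trade-off and not a plain correction.

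A reader might also take 4 to 8 points as the expected inflation. The documents give no over-report rate, and the calculation places all of it in one arm.

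**Conclusion.** The concern holds in limited form. The article asserts blinded interviewers and concedes only un-blinding that participants start, while scheduling questions likely to reveal the arm if those interviewers ask them. The self-reported secondary and mediator outcomes are thereby open to interviewer bias, and separately to participant reporting bias that blinding cannot remove. The conclusion rests on the inference that the follow-up interviewers administer the items.

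The size is unknown. The 4.2 to 8.4 points depend on assumed over-reporting of 10% to 20% in one arm at 58% true linkage. It would be wrong to extend the point to the laboratory viral load result. The change is worth making because it is cheap and protects outcomes that carry the mediation and cost-effectiveness aims.

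**What to change.** 1. Put the contamination and intervention-cost items in a final module of the electronic questionnaire, opened only after the linkage, ART, adherence and retention items are locked.
2. Where existing staffing allows, avoid sending the same interviewer to a participant at six and 12 months.
3. Amend the blinding statements in Data collection procedures and measures and in Limitations to say that the instrument itself may un-blind interviewers.
4. For linkage, ART start and retention, report in both arms an analysis that counts only events verified by clinic record, clinic card or observed ARVs, with unverified self-report not counted as an event. Show it beside the analysis that includes self-report. Do not substitute self-report whenever no record is found.

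The cost is a reordered form, two edited statements and one further analysis, since computerized interviews and record abstraction are already planned. The interviewer change depends on staffing. The downside is that visits to non-participating clinics without a card may be missed in the verified analysis; the self-report-inclusive analysis beside it shows how much this could matter.
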